**Fig. 1 Fig1:**
[figure not shown]
Care processes and analysis of study arms. ^*^Analyses will include all patients identified in the VA dashboard

Approximately 30 days after starting the medication, a member of the study team calls the patient to assess for medication side effects. If the patient tolerates the medication, follow-up labs will be scheduled to reassess the patient’s basic metabolic panel. However, if the patient has side effects or concerns, the patient will receive a follow-up phone call and assessment by the pharmacist to determine if empagliflozin should be continued. If the one-month lab results come back abnormal, the patient will have a follow-up outreach to determine the appropriate course of action and to engage with the patient’s primary care team. If the lab results are stable and within normal limits, the patient will receive a letter with their lab results and continued care from their primary care team. Patients in the control arm will receive usual care while the first iteration of this program is ongoing and may be prescribed an SGLT2i, if recommended by their care team.

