### Outcomes

Our primary outcome is initiation of an SGLT2i among patients deemed candidates for SGLT2i as determined by the VA dashboard. Patients who filled an SGLT2i at any point during the study timeframe, as determined by electronic health record data, will be considered to have initiated the medication.

Secondary outcomes will include adherence to the medication 12 months after initial prescribing (defined by refills of their SGLT2i), as well as various process and safety measures, such as the number and percent of patients who obtained metabolic labs after SGLT2i initiation, abnormal lab results, including acute kidney injury, and defined reasons for declining or stopping the medication (including low blood pressure/hypotension and hypoglycemia). Secondary outcomes will also include the proportion of patients who decline the intervention and later obtain an SGLT2i from another source (which will be reported as a descriptive statistic only as Veterans in the usual care, unlike those in the intervention arm, cannot crossover to the alternative arm). In addition, we will examine the progression of kidney disease, defined as a 40% reduction in eGFR sustained for at least two measures. We will also measure the number of times eGFR is assessed as this may affect outcome ascertainment.

Exploratory outcomes will include rates of all-cause hospitalizations, initiation of dialysis, and major adverse cardiac events (nonfatal myocardial infarction, nonfatal stroke, and hospitalization for heart failure).

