### Analysis

We will assess balance in baseline clinical and demographic characteristics between the two study arms with chi-square tests for categorical variables (e.g., patient sex) and Kruskal-Wallis test assuming unequal variances for continuous variables (e.g., patient age, baseline eGFR as calculated by the final serum creatinine concentration before the index date via the most recent CKD-EPI equation) [28]. The primary and secondary outcomes, the proportion of initiation of SGLT2i or proportion with a safety or process measure, respectively, will be compared between the study arms via the Two-Sample Proportions test. For binary exploratory outcomes, such as initiation of dialysis, major adverse cardiac events, and progression of kidney disease, we will also compare proportions between the arms via Two-Sample Proportions test. When these binary outcomes have an associated time of occurrence, Kaplan-Meier analysis will be used to assess the cumulative incidence of these events. We will use logistic regression and Cox proportional hazards models for adjusted analyses accounting for patient medical and demographic characteristics for binary and time-till-event outcomes. A Type-I-Error rate of 0.05 will be used for the primary outcome to declare significance and we will report the associated 95% confidence interval. Secondary outcomes will also use a p-value of < 0.05 and 95% confidence intervals.

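### Kidney disease progression is confirmed by a count of eGFR measures with no minimum interval, so one reversible acute kidney injury episode can qualify

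*Protocol article*

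**What the plan says.** Under Outcomes, progression of kidney disease is "defined as a 40% reduction in eGFR sustained for at least two measures". The only content given to the idea of a sustained fall is the number of measures. The section states no interval between them and no rule on values taken in hospital or during acute illness.

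The same section lists "abnormal lab results, including acute kidney injury" among the safety measures, so AKI is a separate outcome. It then adds: "We will also measure the number of times eGFR is assessed as this may affect outcome ascertainment".

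Data collection says that clinical outcomes come from the VA electronic health record. No eGFR schedule common to both arms is stated. The Intervention section (text after Fig. 1) describes one programme-scheduled laboratory check, about a month after starting: "If the patient tolerates the medication, follow-up labs will be scheduled to reassess the patient’s basic metabolic panel". For the other arm it says: "Patients in the control arm will receive usual care while the first iteration of this program is ongoing".

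Under Analysis, progression is compared between arms with an unadjusted two-sample proportions test. Kaplan-Meier curves are used where event times exist, and logistic or Cox models adjust for patients' clinical and demographic features. No analysis is said to use the eGFR count.

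**The concern.** A confirmation rule for a chronic kidney outcome is there to separate lasting loss from a temporary fall. A rule that counts measures does this only if the measures are spread out in time. With fixed visits months apart, two consecutive low values would imply duration. With record-based labs they need not, because testing clusters when a patient is ill and both values can come from one week.

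Three consequences follow:

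- Patients whose function recovers fully are recorded as having progressed.
- If such false events are equally common in both arms, they pull the relative effect towards no difference and add noise to the absolute difference.
- If AKI itself differs between arms, part of that difference reappears as a difference in progression. Two outcomes reported as distinct then partly repeat each other.

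The primary outcome, SGLT2i initiation, is not affected.

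**Working it through.** **Is there a figure to reproduce?** No. The article gives no AKI rate, progression rate, event count or sample size. Every rate below is an assumption, used only to show how the rule behaves.

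**Reading adopted.** The reading most favourable to the plan is used: a patient qualifies only if two consecutive eGFRs are both at least 40% down, with no recovered value between them.

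**Assumed inputs.** Follow-up is one year. No patient has lasting loss. Transient falls of at least 40% occur at rate *r* per patient-year, last *D* days and recover fully. Routine labs number *L* per year at random times. In a share *q* of episodes a lab is drawn at a random time in the episode and repeated 0 to 5 days later. Each cell simulates 1,000,000 patients.

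**Usual care: share without lasting loss who meet the definition**

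| *r* | *D* | *L* | *q* | no gap | gap ≥ 28 days | gap ≥ 90 days |
|---|---|---|---|---|---|---|
| 0.05 | 14 | 3 | 0.3 | 1.25% | 0.01% | 0.00% |
| 0.05 | 30 | 3 | 0.3 | 1.42% | 0.01% | 0.00% |
| 0.10 | 30 | 4 | 0.5 | 4.61% | 0.08% | 0.03% |

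Per 1,000 patients, that is about 12 to 46 false events with no gap and fewer than 1 with either gap.

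**Hand check of the no-gap column.** The repeat comes on average 2.5 days after the first lab, so both values fall inside the episode with probability 1 − 2.5/*D*. The false-event rate is roughly *r* × *q* × (1 − 2.5/*D*):

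- 0.05 × 0.3 × (1 − 2.5/14) = 0.0123, or 1.23%
- 0.05 × 0.3 × (1 − 2.5/30) = 0.0138, or 1.38%
- 0.10 × 0.5 × (1 − 2.5/30) = 0.0458, or 4.58%

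These agree with the simulation; chance routine labs account for most of the small remainder. The check also shows that the no-gap figure is close to a product of the assumed inputs. The contrast between columns is therefore more informative than the level.

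**Carry-over of an AKI difference.** By the same formula, each 0.01 per patient-year difference in episode rate between arms becomes a progression difference of 0.01 × 0.3 × 0.821 = 0.25 percentage points in the first scenario and 0.01 × 0.5 × 0.917 = 0.46 in the third.

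**Extra one-month panel.** In the intervention arm, patients who start get one added lab, repeated within a week in 80% of cases if low. No-gap rates:

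| scenario | control | 30% start | all start |
|---|---|---|---|
| 1 | 1.25% | 1.27% (+0.02) | 1.34% (+0.09) |
| 2 | 1.42% | 1.48% (+0.06) | 1.64% (+0.22) |
| 3 | 4.61% | 4.67% (+0.06) | 4.89% (+0.28) |

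The simulation standard error of such a difference is √(2*p*(1−*p*)/1,000,000), or about 0.016 to 0.030 percentage points. The 30% column is therefore only slightly above simulation noise.

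**The case against.** The strongest objection is that a journal article condenses, and that an interval or inpatient rule may stand in a full protocol or analysis plan that is not shown. That may be so. But the article does more than stay silent: it prints a threshold and a confirmation rule, and the rule as printed misclassifies if followed. That part of the concern survives.

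A second objection is that the ascertainment problem is already acknowledged, since eGFR assessments will be counted. This deserves credit. But no use of the count in the comparison is stated, and counting tests does not separate acute from lasting falls.

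Several stronger readings are tempting and should not be drawn:

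- *That any two low values qualify, even with recovery between them.* The word sustained most naturally means consecutive low values, and the check above assumes that.
- *That the intervention arm's extra testing seriously biases the comparison.* The scheduled panel applies only to programme patients who start and tolerate the drug, and one panel cannot alone satisfy a two-measure rule. After an abnormal result the text says only "If the one-month lab results come back abnormal, the patient will have a follow-up outreach to determine the appropriate course of action"; a repeat lab is plausible but not stated. Controls may receive an SGLT2i from their own care team, and the Discussion treats laboratory testing after starting as routine, so control initiators may be tested too.
- *That the 40% fall is measured from one unreliable creatinine.* The phrase "baseline eGFR as calculated by the final serum creatinine concentration before the index date" describes a variable in the baseline balance check. It is not stated to be the reference for progression, and averaging two values would be a preference.
- *That 90 days is required.* In the check, 28 days already removes nearly all false events.

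**Conclusion.** The concern holds for the definition itself. As printed, two consecutive low eGFRs within one reversible AKI episode count as progression, and the same episode can also count as AKI. That such misclassification is possible follows from the text; its size does not. Under the stated assumptions it is about 1.3% to 4.6% of patients without lasting loss over one year, falling to under 0.1% with a gap of 28 days or more. The success of 28 days depends partly on the assumed episode length of 14 to 30 days; slower recovery would need a longer gap.

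Unequal detection from the one-month panel is secondary, at about 0.02 to 0.3 percentage points under the same assumptions. The documents do not support a claim that it would by itself create an apparent kidney harm or hide a benefit.

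The definition should be corrected before the kidney results are analysed. The matter is not critical: Outcomes places progression with the secondary outcomes, Analysis names it among the exploratory ones, and the primary comparison is untouched.

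**What to change.** Reword the outcome so that progression requires:

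- a fall in eGFR of at least 40% from a stated pre-index baseline;
- confirmation by a second value at least a prespecified interval later (at least 28 days; 90 days is one acceptable and more conservative choice);
- no intervening value above the threshold;
- no inpatient value as a qualifying measure.

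Apply the rule identically in both arms, and state whether the first or the confirming value dates the event in the Kaplan-Meier and Cox analyses. Say what the eGFR count is for. A descriptive table by arm would be enough; because the count arises after assignment, adjusting for it would not be a clean repair.

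The change affects only the outcome algorithm and uses the same record data, with no new visits or tests. The cost is fewer qualifying events, hence less precision, and follow-up time for confirmation: a fall first seen near the end of follow-up cannot be confirmed. Patients with few outpatient labs will also contribute fewer events.

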### Data collection

All process data are collected through a tracking app developed specifically for this project. Clinical outcome data are collected and stored in the VA electronic health record.

### Analysis

We will assess balance in baseline clinical and demographic characteristics between the two study arms with chi-square tests for categorical variables (e.g., patient sex) and Kruskal-Wallis test assuming unequal variances for continuous variables (e.g., patient age, baseline eGFR as calculated by the final serum creatinine concentration before the index date via the most recent CKD-EPI equation) [28]. The primary and secondary outcomes, the proportion of initiation of SGLT2i or proportion with a safety or process measure, respectively, will be compared between the study arms via the Two-Sample Proportions test. For binary exploratory outcomes, such as initiation of dialysis, major adverse cardiac events, and progression of kidney disease, we will also compare proportions between the arms via Two-Sample Proportions test. When these binary outcomes have an associated time of occurrence, Kaplan-Meier analysis will be used to assess the cumulative incidence of these events. We will use logistic regression and Cox proportional hazards models for adjusted analyses accounting for patient medical and demographic characteristics for binary and time-till-event outcomes. A Type-I-Error rate of 0.05 will be used for the primary outcome to declare significance and we will report the associated 95% confidence interval. Secondary outcomes will also use a p-value of < 0.05 and 95% confidence intervals.

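### The between-arm test is applied to every safety and process measure, but some measures exist or are solicited only in the intervention arm, and lab detection may differ between arms

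*Protocol article*

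**What the plan says.** The Analysis section gives one rule for the secondary measures: "proportion with a safety or process measure, respectively, will be compared between the study arms via the Two-Sample Proportions test". It adds: "Secondary outcomes will also use a p-value of < 0.05 and 95% confidence intervals". It names no exception.

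The Outcomes section lists the measures to which this applies. On laboratory follow-up they include "the number and percent of patients who obtained metabolic labs after SGLT2i initiation, abnormal lab results, including acute kidney injury". A further item in that list covers the grounds that patients give: "defined reasons for declining or stopping the medication (including low blood pressure/hypotension and hypoglycemia".

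The Data collection section names two sources. For process measures: "All process data are collected through a tracking app developed specifically for this project". For clinical outcomes: "Clinical outcome data are collected and stored in the VA electronic health record".

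The Intervention section, including the text below Fig. 1, describes the letter, the scheduling call, the pharmacist visit and the later follow-up as steps of the programme. About 30 days after the start, "a member of the study team calls the patient to assess for medication side effects". It continues: "If the patient tolerates the medication, follow-up labs will be scheduled". Controls have usual care meanwhile, and their own care team may prescribe an SGLT2i.

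The Outcomes section makes one measure descriptive: the share of patients who decline the intervention and later get the drug elsewhere. The reason given is that this cannot happen under usual care. The same section plans to count eGFR measurements because their number could influence what is detected. The Analysis section does not mention that count.

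**The concern.** A two-sample test of proportions needs the same event to be observable in both arms, by means that are at least comparable. Several of the listed measures are by-products of the programme's own contacts. A patient who is never offered anything cannot give a reason for declining it. A patient who is telephoned and asked about side effects will report more than one who is not asked. A patient given a scheduled metabolic panel has an extra opportunity for an abnormal value to be found.

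At stake is the safety message of the trial. If the rule is followed as written, a p-value below 0.05 on stopping for hypotension or hypoglycemia, or on abnormal labs, could be read as harm from the outreach strategy when some or all of the difference reflects who was asked or tested. The primary outcome, SGLT2i fills taken from the electronic health record, is not touched by this point.

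**Working it through.** The article gives no sample size, event rate or testing rate, so there is no figure of its own to reproduce. The check has two parts.

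**1. Each measure traced to its source**

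| Measure | Intervention arm | Control arm | Between-arm test |
|---|---|---|---|
| Reasons for declining | Given in response to the programme's offer | No offer, so nothing to decline | Undefined, or zero by design |
| Reasons for stopping | Asked about at the 30-day call | Starters can stop, but no structured source is described | Solicited versus unsolicited |
| Other measures recorded only in the app | Tracking app | No control-arm use of the app is described | No described control value |
| Abnormal labs, acute kidney injury | Health record, plus a programme-scheduled panel | Health record, usual-care testing | Computable, but detection may differ |
| Labs obtained after starting | Programme-scheduled and routine | Routine only | Computable; partly a genuine programme effect |

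For declining, the outcome depends on the denominator. Among patients offered the programme, the control proportion is 0/0. Among all dashboard-identified patients, the set named in the Fig. 1 footnote, it is 0 by construction. Neither can be tested meaningfully.

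For labs, the scheduled panel is also conditional on tolerance as written. Patients with side effects go to a pharmacist assessment, and no panel is stated for them. Detection can therefore vary within the intervention arm as well.

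**2. How large could differential lab detection be?**

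All inputs here are assumptions. Let r be the true risk of an abnormal result among starters, equal in both arms, and d the share of events detected. The observed proportion is r × d.

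- r = 5%, d = 90% in the intervention arm: 0.05 × 0.90 = 4.5%.
- r = 5%, d = 50% in controls: 0.05 × 0.50 = 2.5%. Ratio 4.5/2.5 = 1.8.
- r = 5%, d = 70% in controls: 0.05 × 0.70 = 3.5%. Ratio 4.5/3.5 ≈ 1.3.
- r = 10%: 9% versus 5–7%. The ratios are unchanged, because r cancels.

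Chance of a significant excess in the intervention arm (two-sided 0.05, equal arms, r from 5% to 10%, detection 90% versus 50–70%):

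| Starters per arm | Lowest (r = 5%, 90% v 70%) | Highest (r = 10%, 90% v 50%) |
|---|---|---|
| 200 | 7% | 35% |
| 500 | 12% | 70% |
| 1000 | 21% | 94% |

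With equal detection this chance is 2.5%.

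**A separate effect that must not be confused with detection.** If the denominator is all listed patients, more starts alone can produce a difference. Assume 1000 patients per arm, 30% starting in the intervention arm and 10–20% in controls, a risk of 5–10% per starter, and equal detection. At 5% risk the observed proportions are 0.30 × 0.05 = 1.5% versus 0.5–1.0%; at 10% risk they are 3% versus 1–2%. The chance of a significant excess is then 17% to 89%. That excess would be a consequence of greater drug use and not an artefact of testing.

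**The case against.** The strongest reply is that clinical outcomes come from the electronic health record, which covers both arms. Controls may start and stop an SGLT2i, and the Discussion treats lab testing after a start as routine. Lab and kidney-injury proportions can therefore be calculated in both arms. This stands. A reader might infer that all these tests are impossible, or that no control denominator exists for stopping. The documents do not support that: only reasons for declining are structurally absent in controls.

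Second, a higher share with labs obtained is what a monitoring programme should produce. This also stands. It is a process effect and not detection bias. Its weakness is that the denominator, starters, is formed after assignment.

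Third, the protocol already makes one such measure descriptive and already counts eGFR measurements, and an article may leave measure-by-measure handling to an analysis plan. This stands only in part. The article states the test for these measures without exception, and neither safeguard is carried into its Analysis section.

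Fourth, the direction is not settled. Tying the panel to tolerance could lower detection in the intervention arm, and an excess over all listed patients could be a real drug effect. This stands as a limit on what can be claimed.

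**Conclusion.** The point holds in two parts of different strength.

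For reasons for declining, the planned test has no valid control value. For stopping reasons and other app-only measures, it would compare active enquiry with whatever usual care happens to record, since no control-arm source is described. This follows from the text and needs no assumption about rates.

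For abnormal labs and acute kidney injury, the test can be done but is open to differential detection. The assumed scenarios give a spurious ratio of about 1.3 to 1.8 with no true difference. The real size, and even the net direction, depends on control-arm testing rates that the article does not give.

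A reader might infer that the intervention arm is bound to show more harm, or that any safety result would be an artefact. The documents do not establish either. Nor do they say that process data are held solely in the app; they say only that such data are collected through it.

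The matter should be corrected, but it concerns secondary outcomes only.

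**What to change.** Amend the Analysis section as follows.

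- Report reasons for declining, programme-solicited reasons for stopping and other app-only measures descriptively, for the intervention arm alone. This extends the treatment that the Outcomes section already gives to one measure.
- Limit between-arm tests to outcomes ascertained from the health record in both arms, in all dashboard-identified patients from the index date.
- Present abnormal-lab and kidney-injury comparisons next to testing frequency by arm, using the eGFR count already planned, and add an analysis that accounts for it.
- Keep labs obtained as a between-arm process comparison, with its denominator stated.
- Optionally, add health-record-coded acute kidney injury, hypotension or hypoglycemia as a sensitivity analysis that depends less on programme contact.

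The cost is wording, use of a count already being collected, and one health-record query if the optional analysis is adopted. The programme-only measures lose a p-value that could not be interpreted. The drawback of the coded-event analysis is that it does not capture milder events, so it should supplement the lab-based comparison and not replace it.

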## Methods

### Study design and setting

The VA is divided into different regional systems of care across the U.S. called Veterans Integrated Service Networks (VISNs). This multicenter interventional study focused on the Midwest VISN, which includes 8 VA health systems across Minnesota, Iowa, North Dakota, South Dakota, and Nebraska. Eligible Veterans are assigned to either a targeted pharmacy intervention or usual care. The study began in February 2022 and will continue until all eligible Veterans in the region are offered the intervention, which is anticipated to be in 2025.

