### Patient selection and randomization

As part of their Academic Detailing Diabetes Campaign and to monitor SGLT2i initiation, the VA developed a diabetes dashboard to identify patients who would benefit from an SGLT2i. The dashboard includes the above inclusion criteria and several other demographic and clinical variables. The dashboard is updated daily to reflect eligible patients. One included variable in the dashboard is patients’ social security number. Due to the finite availability of resources, we have utilized a pseudo-randomization of eligible Veterans to determine which Veterans within the VISN receive the intervention first, providing a natural comparison group in those Veterans who will be intervened upon later. For this study, patients with an odd social security number are put in the intervention arm, while those with an even social security number serve as the control. Patient lists will be extracted from the VA dashboard at fixed time points throughout the study and will be considered the dates of randomization. The controls will receive usual care until all eligible Veterans in the odd-numbered group have received the intervention. At that time, even-numbered Veterans will also begin to receive the intervention.

The intervention will be implemented in a rolling fashion, beginning with patients at the Minneapolis VA health system, and other clinics will be subsequently added as outreach is being completed.

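### The primary test pools all health systems and list dates; stratifying by both would gain a little precision at almost no cost

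*Protocol article*

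**What the plan says.** All references are to the protocol article.

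- **Primary method (Analysis).** The proportion initiating an SGLT2i "will be compared between the study arms via the Two-Sample Proportions test". On the error rate: "A Type-I-Error rate of 0.05 will be used for the primary outcome to declare significance". A 95% confidence interval is to be reported.
- **Adjusted models (Analysis).** Logistic and Cox models are planned as "adjusted analyses accounting for patient medical and demographic characteristics for binary and time-till-event outcomes". Neither health system nor list date is named.
- **Sites (Study design and setting).** The study covers one regional network, "which includes 8 VA health systems across Minnesota, Iowa, North Dakota, South Dakota, and Nebraska". It began in February 2022 and is expected to run to 2025.
- **Index dates (Patient selection and randomization).** "Patient lists will be extracted from the VA dashboard at fixed time points throughout the study and will be considered the dates of randomization".
- **Roll-out (same section).** "The intervention will be implemented in a rolling fashion, beginning with patients at the Minneapolis VA health system", with other clinics added later.
- **Allocation (same section).** "patients with an odd social security number are put in the intervention arm, while those with an even social security number serve as the control". No stratification or blocking is described.
- **Outcome window (Outcomes).** A fill at any time in the study period counts as initiation. No fixed window per patient is given.

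**The concern.** Site and list date are both likely to predict the primary outcome. Patients on early lists have longer to record a fill than patients on late ones. The Background and Discussion describe prescribing that is expected to shift after recent guideline changes, so background uptake plausibly depends on calendar time. Sites join in sequence and two pharmacists carry out the visits, so the delay to outreach can differ between sites and lists.

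Both factors are fixed at the index date, before any outreach, which makes them natural stratification factors. A pooled test leaves the variation they explain in the error term. It also makes no correction if odd-numbered patients happen to be over-represented on lists with high or low uptake. At stake is the precision of the primary estimate, not its validity.

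**Working it through.** **Is there a design figure to reproduce?** No. The article gives a type I error rate of 0.05 but no sample size, power, control rate, effect size or between-site spread. Everything below except 0.05 and the 8 health systems is an assumption.

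**Step 1. Share of outcome variance lying between strata.**

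Share = (variance of stratum rates) / [p(1 - p)], where p is the mean rate. For 8 equal strata with rates evenly spaced over a range R, the variance is (R/7)^2 x (8^2 - 1)/12 = (R/7)^2 x 5.25.

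- 15-25%, p = 0.20: 0.00107/0.16 = 0.0067
- 10-30%, p = 0.20: 0.00429/0.16 = 0.0268
- 5-35%, p = 0.20: 0.00964/0.16 = 0.0603
- 2-50%, p = 0.26: 0.02469/0.1924 = 0.1283

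If stratifying removed the whole share, the confidence interval would shrink by a factor of about sqrt(1 - share). This is sqrt(1 - 0.0603) = 0.969 for the 5-35% spread and sqrt(1 - 0.1283) = 0.934 for 2-50%, or intervals about 3% and 7% narrower.

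**Step 2. Simulated size and power.** There were 20,000 replicates with 8 equal strata and a two-sided 0.05 level. Each patient was allocated independently 50:50, as parity would do. The assumed effect was +10 points in every stratum. Sample size was set for about 80% power with the pooled test: 296 per arm at a mean control rate of 20%, and 336 per arm at 26%.

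| Control rates across strata | Type I error, pooled | Type I error, CMH | Power, pooled | Power, CMH | Difference in power (points) |
|---|---|---|---|---|---|
| 20% in all | 5.0% | 5.0% | 80.4% | 80.0% | -0.4 |
| 15-25% | 5.2% | 5.2% | 80.7% | 80.2% | -0.5 |
| 10-30% | 4.9% | 4.9% | 80.7% | 81.0% | +0.4 |
| 5-35% | 5.0% | 5.1% | 80.1% | 82.0% | +1.8 |
| 2-50% | 4.8% | 4.7% | 80.6% | 84.3% | +3.8 |

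Differences are taken before rounding. The simulation standard error of a single power figure is sqrt(0.8 x 0.2/20,000) = 0.0028, or about 0.3 points.

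**Step 3. Bias.** With no true effect, the mean pooled difference was within 0.0003 of zero in every scenario. With a true difference of 0.10 it was 0.100.

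**Step 4. Contrast case.** With allocation forced to exactly 1:1 within each stratum, the pooled test became conservative: type I error was 4.6% at 5-35% and 3.7% at 2-50%, against 5.2% for CMH in both. The article does not describe this kind of allocation.

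**The case against.** The strongest objection is that nothing in the stated test is wrong. Parity is a fixed patient trait that acts like simple allocation, so there is no stratified randomization for the analysis to mirror. The pooled test keeps its size, its standard error is correct for its own estimator, and chance imbalance is already covered by the 5% level and the confidence interval. No power target is stated that a small loss would threaten. The article is condensed, and the full covariate list may sit in a plan that is not shown. All of this stands, and it limits the point to efficiency.

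Four stronger readings are tempting but not supported:

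- **Staggered entry and unequal follow-up bias the comparison or inflate type I error.** Odd and even patients on a list share its date, and parity should be unrelated to site or date, so these factors balance in expectation. The simulation agrees.
- **The pooled standard error is too wide.** That holds only for exact balance within strata. Under parity allocation the pooled standard error is merely larger than a stratified analysis would give.
- **Stratifying removes the effects of follow-up length and secular uptake entirely.** It holds site and list date equal between arms. Delay to outreach affects only the intervention arm, and the effect may itself vary with follow-up. Stratification removes neither.
- **The adjusted models exclude site and list date.** The article does not name them, but neither does it rule them out.

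The objection does not dispose of the primary test itself. The article names that test outright, so a fuller covariate list for the adjusted models would not change it.

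**Conclusion.** The point holds as a low-severity efficiency improvement. The stated primary analysis is valid and unbiased under parity allocation, but it ignores two factors, known at baseline, that probably predict the outcome.

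The loss is about 0 to 2 power points for stratum control rates spanning up to 5-35%, and about 4 points for an extreme 2-50% spread. These figures rest on assumed rates, 8 equal strata, a constant +10-point effect and a trial sized for about 80% power. If the trial is much larger than that, the gain in power shrinks, although the proportional narrowing of the confidence interval does not. If strata are similar, stratifying gains nothing and may cost up to about half a power point.

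**What to change.** 1. Make the primary analysis a Mantel-Haenszel risk difference with 95% confidence interval and CMH test, stratified by health system and the date of the patient's first list.
2. Use the first list because the article does not say whether a patient can reappear on later ones. Later membership could depend on arm, since patients already started on treatment would no longer qualify.
3. State in advance a rule for merging sparse strata that makes no reference to outcomes.
4. Include the same two factors in the logistic models, and stratify the Cox models by them.
5. Keep the pooled two-sample test as a sensitivity analysis.

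The cost is a change of wording, slightly more analysis work and possibly some merging of small lists. Health system and list date should be available from the list extraction itself, though the article does not say how they are stored. No change to conduct or data collection is expected.
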